#### Statistical analysis

Data from our previous 3-month study in prostate cancer patients indicates that the standard deviation for change in our primary outcome of sexual health equates to ~22 points on the QLQ-PR25 sexual activity domain [26]. We observed the mean change after the intervention to differ between exercise and usual care groups by ~11 points [26]. There is no available evidence comparing changes in sexual health between exercise and psychosexual interventions. However, data from previous psychosexual interventions in prostate cancer patients indicates changes of a moderate standardised effect (*d* = 0.5) in sexual health following the psycho-educational interventions [32,33]. We have based sample size calculations on the assumption that there will be an additive effect of exercise and psychosexual therapies. A priori, 64 participants per group will be required to achieve 80% power at an alpha level of 0.05 (two tailed), and to demonstrate a difference between the three groups in sexual health at the end of the intervention. Previous experience in exercise and psychosexual therapy trials indicates an attrition rate of up to 20% over the intervention period. Therefore, to adequately ensure that we have sufficient participant numbers at the end of the intervention, 240 participants will be randomised to the study arms. A sample size of 240 will also provide us with sufficient power to detect a moderate standardised effect (*d* = 0.5) in our secondary outcomes. Based on previous experience we anticipate a further attrition rate of up to 20% over the follow-up period. Therefore, the sample size will provide 87% statistical power to detect differences between the Exercise group and the Exercise + Psychosexual group at follow-up (*d* = 0.5; n = 77 per group as the usual care group will be split between the two interventions for the prospective cohort study component of this project).

Data will be analysed using an intention-to-treat approach with maximum likelihood imputation of missing values. Analyses will include standard descriptive statistics, Student’s t-tests, chi-square, correlation and regression, and two way (group × time) repeated measures ANOVA (or ANCOVA as appropriate) to examine differences between groups over time. Clinically relevant covariates will be included in analyses. All tests will be two-tailed and an alpha level of 0.05 will be applied as the criterion for statistical significance.

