
1. Examine the efficacy of exercise as a therapy to aid in the management of sexual dysfunction in men with prostate cancer.

2. Determine if combining exercise and brief psychosexual self-management results in more pronounced improvements in the sexual health of men with prostate cancer.

3. Assess if any benefit of exercise and brief psychosexual self-management on sexual dysfunction in men with prostate cancer is sustained long term.

We will evaluate three main hypotheses: 1) Compared with usual medical care, exercise will improve sexual health in men with prostate cancer who are concerned by sexual dysfunction. We theorise that exercise will improve masculine self-esteem, quality of life, psychological distress, fatigue, body composition, body image and physical function, culminating in increased sexual health; 2) When exercise and brief psychosexual self-management are combined, improvements in sexual health will exceed those observed in usual medical care and exercise therapy alone. We theorise that brief psychosexual self-management will further enhance improvements in sexual health through increasing men’s ability to better self-manage their well-being and sexual dysfunction (i.e. enhanced uptake of pharmacologic management of erectile dysfunction); and 3) Improvements in sexual health will be sustained 1 year after completion of the exercise and combined exercise and psychosexual interventions. We hypothesise that the theoretically based interventions will prompt behavioural change that leads to sustained improvements in sexual health.

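### The 80% power is attached to a three-group difference, but 64 per group is the size for a single unadjusted two-arm comparison; the number is right for each pair and the stated target is wrong

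*Protocol article*

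**What the plan says.** All the inputs are in the Statistical analysis section of the protocol article.

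- Spread: "the standard deviation for change in our primary outcome of sexual health equates to ~22 points on the QLQ-PR25 sexual activity domain".
- Exercise against usual care: "We observed the mean change after the intervention to differ between exercise and usual care groups by ~11 points".
- Psychosexual component: earlier data "indicates changes of a moderate standardised effect (*d* = 0.5) in sexual health following the psycho-educational interventions".
- Combination: "We have based sample size calculations on the assumption that there will be an additive effect of exercise and psychosexual therapies".
- Result: "A priori, 64 participants per group will be required to achieve 80% power at an alpha level of 0.05 (two tailed"), with the target given as "to demonstrate a difference between the three groups in sexual health at the end of the intervention". Attrition of up to 20% brings the total to 240 randomised, 80 per arm.
- Significance level: "All tests will be two-tailed and an alpha level of 0.05 will be applied as the criterion for statistical significance".

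The Background section sets the hypotheses separately. Hypothesis 1 is that exercise is better than usual care. Hypothesis 2 is that with the combination, "improvements in sexual health will exceed those observed in usual medical care and exercise therapy alone". No section says that both must succeed for the trial to count as positive.

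**The concern.** A power figure means something only together with the test it belongs to. The sentence gives 80% and names a difference among three groups. That can be read as the overall three-group test, or as all three arms being told apart. Under the protocol's own assumptions neither has 80% power: the first is far higher and the second is lower.

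What is at stake is interpretation. Suppose both effects are real and one adjacent contrast misses significance. A reader who took the 80% to cover the whole three-arm pattern would think that outcome less likely than it is, and might over-read it as evidence of no effect. The sentence also leaves open whether 0.05 is meant for one three-group test or for each pair.

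**Working it through.** **Inputs (Statistical analysis section).** SD of change 22; difference 11, so d = 11/22 = 0.5; psychosexual effect d = 0.5; additive effects; two-sided alpha 0.05; 64 completers per arm. Additivity puts the arm means at 0 (Usual Care), 0.5 (Exercise) and 1.0 (Exercise + Psychosexual) SD. A common SD in all arms is assumed.

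**1. The stated figure reproduces as a two-arm test.** Normal approximation: n = 2(1.960 + 0.842)²/0.5² = 62.8, so 63 per group. With the t distribution n = 63.8, so 64, and power at 64 is 80.1%. Attrition: 3 × 64 = 192, and 192/0.8 = 240. Both stated sizes are correct for one pairwise comparison.

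**2. Overall three-group test.** The grand mean is 0.5, so f = √[(0.5² + 0² + 0.5²)/3] = 0.408. With 192 men the noncentrality is 192 × 0.408² = 32 on 2 and 189 degrees of freedom. Power is 99.95%, and 80% would need only about 21 per group. So 64 did not come from this test under the additive means.

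**3. Each hypothesis alone.**
- Hypothesis 1, Exercise against Usual Care, d = 0.5: 80.1%.
- Hypothesis 2 needs Exercise + Psychosexual to beat Exercise (d = 0.5, 80.1%) and Usual Care (d = 1.0, 99.99%). The joint probability is at least 0.8015 + 0.9999 − 1 = 0.801, so about 80%.

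**4. Both adjacent contrasts together.** Each difference has variance 2σ²/n. They share the Exercise arm with opposite sign, so their covariance is −σ²/n and their correlation −0.5. At n = 64 each standardised mean is 0.5/√(2/64) = 2.83, which exceeds 1.96 by 0.87. The bivariate normal probability that both are significant is 62.2%. Simulated t-tests give 61.2%, or 61.3% with the variance pooled over three arms. This is below the independence product 0.801² = 64% because of the negative correlation. Requiring Exercise + Psychosexual better than Usual Care as well leaves it at 61.2%. The chance of at least one is 0.802 + 0.802 − 0.612 = 0.99.

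**5. Dependence on attrition (simulated t-tests).**

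| Completers per arm | Loss from 80 | Both adjacent contrasts |
|---|---|---|
| 64 | 20% | about 61% |
| 72 | 10% | about 70% |
| 80 | none | about 76% |

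**6. Familywise error.** If the three arms do not differ, three pairwise tests at 0.05 on one outcome give at least one false positive about 12% of the time (simulated at 64 per arm). If pairs are tested only after a significant overall test, the rate is 5%. If only one pair is truly equal, only one false positive is possible, and it is tested at 0.05, so three arms need no further correction. Under additivity the gate costs almost nothing: simulated joint power with it is still 61.2%.

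**The case against.** The strongest reply is that nothing is miscalculated and that the pairwise reading is the natural one. The inputs are pairwise, a two-tailed test suits a t-test better than an overall F-test, t-tests are among the listed analyses, and the follow-up power is openly pairwise: Exercise against Exercise + Psychosexual at d = 0.5 with 77 per group, stated as 87% and recomputed as 86.9%. Additivity then explains why one size serves both adjacent contrasts. Powering each hypothesis on its own is ordinary practice. All of this stands. It shows what the authors probably meant, but it does not make the sentence say it: the target written down is a difference among three groups.

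Two stronger readings are tempting and should be resisted.

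- A reader might infer that the trial is underpowered, or that 61% is its true chance of success. The documents do not support this. The hypotheses are listed separately, each has about 80% power, and no rule demands both. The 61% also assumes the full 20% loss, which the protocol gives as an upper limit, and takes no credit for the planned likelihood-based handling of missing data or for covariates.
- A reader might infer that power should be cut for a Bonferroni correction. The protocol plans none, and a multiplicity procedure may sit in an analysis plan that is not shown. The absence of one here is not the finding.

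**Conclusion.** The point holds as a labelling error, not as an error in the sample size. The 64 per group and 240 in total are right for a single pairwise difference of 11 points with SD 22, and about 80% is right for Hypothesis 1 and for Hypothesis 2 taken separately. What is wrong is the target named for the 80%. Under additivity the overall three-group test has over 99% power. Showing both adjacent differences, which is the full ordering of the arms, has about 61% at 64 completers per arm, rising to about 76% if nobody is lost.

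These figures rest on the protocol's own effect sizes, on additivity, on a common SD, and on unadjusted two-sided tests of 0.05 without covariate gain. The 99% depends on additivity in particular: if only one component worked (means 0, 0.5, 0.5 or 0, 0, 0.5 SD), the overall test at 64 per group would have about 83%.

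**What to change.** Restate the sample size sentence along these lines: *64 per group gives 80% power for each single pairwise difference of 11 points (SD of change 22) at two-sided 0.05; power to show both adjacent differences is about 61% at 20% attrition; the overall three-group test has over 99% power under additivity.*

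Add one sentence to the analysis: pairs are tested at 0.05 only after a significant overall three-group test on that outcome. This holds familywise error at 5% instead of about 12% for the three comparisons on one outcome. It does not deal with multiplicity across several outcomes.

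The cost is a rewritten paragraph and a somewhat less favourable figure in print, with no extra patients. The gate is nearly free under additivity. If only one component works it costs the pairwise contrasts some power, because the overall test then passes about 83% of the time.

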## Methods/Design

A single-blinded (investigators blinded to group allocation), three arm, multi-site randomised controlled trial (RCT) design will be used to examine the efficacy of exercise and psychosexual therapies on sexual health in men with prostate cancer. An ‘Exercise’ group will complete the exercise intervention, an ‘Exercise + Psychosexual’ group will complete the same exercise intervention as well as a brief psychosexual self-management intervention and a ‘Usual Care’ group will maintain usual medical care for a period of 6 months. The Usual Care group will be offered participation in the interventions at the completion of the 6-month period (half to receive the Exercise intervention and half the Exercise + Psychosexual intervention). The RCT will be followed by a prospective cohort study examining the long-term impact of exercise versus exercise and brief psychosexual self-management on sexual dysfunction in prostate cancer patients 1 year after the interventions (Figure 1). The study will be guided by the CONSORT statement [40].

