### Participants

Two hundred and forty men (80 subjects per arm) treated for prostate cancer will be recruited by invitation from their attending specialist (oncologist/urologist). Participants will be recruited in Perth, Western Australia; Brisbane, Queensland; Central and North Coasts of New South Wales. Inclusion criteria are: 1) concern about sexual health as assessed by an International Index of Erectile Functioning (IIEF) overall satisfaction score < 8 (i.e. moderately-very dissatisfied) [41] and/or Expanded Prostate Cancer Index Composite (EPIC) sexual bother score > 8 (i.e. small-big problem) [42]; 2) prior/current treatment for prostate cancer including prostatectomy, radiotherapy or ADT; and 3) physician consent. Exclusion criteria are: 1) non-nerve sparing prostatectomy; 2) > 6 months since prostatectomy or completion of radiotherapy or ADT; 3) incontinence defined as requiring the use of > 1 pad in a 24-hour period; 4) already performing regular exercise defined as undertaking structured aerobic or resistance training two or more times per week within the past 3 months; 5) acute illness or any musculoskeletal, cardiovascular or neurological disorder that could inhibit exercise or put participants at risk from exercising; and 6) unable to read and speak English. Eligible subjects will undertake a series of familiarisation sessions and baseline measurements prior to randomisation (Figure 2). The protocol has been approved (ID: 10643 [name]) for all participating centres by the Edith Cowan University Human Research Ethics Committee and all participants will provide written informed consent.

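### The follow-up figures of 77 per group and 87% power count no loss during the usual-care men's delayed intervention; at the plan's own maximum attrition they become about 72 and 84%

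*Protocol article*

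**What the plan says.** The protocol article randomises 240 men, 80 to each of three arms (Participants; Statistical analysis). Its Statistical analysis section gives two attrition rates. For the first period: "Previous experience in exercise and psychosexual therapy trials indicates an attrition rate of up to 20% over the intervention period". For the follow-up period it expects a further loss, again of up to 20%.

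It then states that "the sample size will provide 87% statistical power to detect differences between the Exercise group and the Exercise + Psychosexual group at follow-up", for a standardised effect of 0.5 and "n = 77 per group as the usual care group will be split between the two interventions for the prospective cohort study component".

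Other sections fix the path of the usual-care men:
- Methods/Design: "The Usual Care group will be offered participation in the interventions at the completion of the 6-month period". Half are to receive Exercise and half Exercise + Psychosexual. The cohort comparison is made one year after the interventions.
- Measurements: usual-care men have an extra assessment when their delayed intervention ends.
- Figure 1 caption: the six-month follow-up falls at 12 months for the two immediate arms and at 18 months for usual care.

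**The concern.** The 77 per group pools men with different paths through the study. Men in the two immediate arms pass through two periods before the one-year follow-up: the intervention and the follow-up. Usual-care men pass through three: the control period, the delayed intervention and the follow-up. The stated number treats everyone as having two. For usual-care men, the period in which they actually exercise therefore carries no loss, although the plan's intervention-period rate is drawn from exercise and psychosexual therapy trials.

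The 87% is the only power given for the long-term comparison of the two interventions, which serves the third aim. If the retained number is too high, so is that power.

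**Working it through.** **Inputs, all from the protocol article**
- 240 randomised, 80 per arm (Participants).
- Loss of up to 20% over the intervention period and up to a further 20% over follow-up (Statistical analysis).
- Usual-care men split half and half, so 40 randomised men feed each follow-up group (Methods/Design).
- d = 0.5 and two-sided alpha of 0.05 (Statistical analysis).
- Uptake of the delayed intervention is not given. Full uptake is assumed here.

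**Step 1: reproduce the stated figures**
- Retained per group: 240 x 0.8 x 0.8 / 2 = 76.8, which rounds to 77.
- Power of a two-sample t test with n per group uses the noncentral t distribution with noncentrality d x sqrt(n/2). At n = 77 this is 0.5 x sqrt(38.5) = 3.10, and power is 86.9% (87.3% by the normal approximation).
- Both the 77 and the 87% reproduce. The power is right for 77 men, so the question is only whether 77 men remain.

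**Step 2: count the periods**

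| Men feeding each follow-up group | Randomised | Periods before 1-year follow-up | Retained at 20% per period |
|---|---|---|---|
| Immediate arm | 80 | 2 | 80 x 0.8 x 0.8 = 51.2 |
| Half of usual care, as the plan counts it | 40 | 2 | 40 x 0.8 x 0.8 = 25.6 |
| Half of usual care, as the design describes it | 40 | 3 | 40 x 0.8 x 0.8 x 0.8 = 20.48 |

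- As the plan counts it: 51.2 + 25.6 = 76.8.
- As the design describes it: 51.2 + 20.48 = 71.68, about 72. The difference is about 5 men per group.

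**Step 3: power at the corrected number**
- At n = 71.68 the noncentrality is 0.5 x sqrt(35.84) = 2.99. Power is 84.4% (t test) or 84.9% (normal approximation). Rounding up to 72 gives 84.6% by the t test.
- The drop on the t test is 86.9 - 84.4 = 2.5 percentage points.

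**Step 4: sensitivity to the rate in the delayed intervention**
- With a loss of 10% in that period only: 51.2 + 40 x 0.8 x 0.9 x 0.8 = 74.24 per group, power 85.7%.
- With 17.5% in every period: 80 x 0.825^2 + 40 x 0.825^3 = 54.45 + 22.46 = 76.9, which again rounds to 77.

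**The case against.** The strongest defence is that nothing has been left out. The article describes a randomised trial followed by a cohort study, and ties the split of usual care to the cohort component. On that reading the second 20% covers everything after the randomised stage, including the delayed intervention. The article does not say this, and it fits poorly with the Measurements section and the Figure 1 caption. The first sets the end of the delayed intervention apart as its own assessment. The second places the six-month follow-up of usual-care men six months later than that of the other arms. The same 20% would also have to cover a period six months longer for usual-care men than for the rest.

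A second defence is that both rates are upper limits. This stands in part. Step 4 shows that about 17.5% per period would still leave 77 men, so 72 is the number at the limit and not a fixed expectation. But the plan's 77 was itself computed at the limit in both periods that it counts, so the like-for-like figure is 72.

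Third, the consequence is small. This stands in full. The 240 was set by the end-of-intervention comparison (64 per group, and 80 x 0.8 = 64), not by the follow-up statement.

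**Conclusion.** The point holds as a minor correction. At the plan's own maximum attrition, the long-term comparison keeps about 72 men per group and has about 84% power, against the stated 77 and 87%. This rests on a loss of 20% in each of the three usual-care periods, on full uptake of the delayed intervention, and on a two-sided t test at 0.05 with d = 0.5.

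A reader might infer three stronger things that the documents do not support:
- **That the long-term comparison is underpowered.** With full uptake, power stays above the 80% used for the main comparison. Power would fall below 80% only if uptake were under about 61%: the t test needs about 63.8 per group, and (63.8 - 51.2) / 20.48 is about 0.61. The article gives no uptake rate, so any such value is an assumption. It is also not settled that a man who declines would leave an intention-to-treat analysis with maximum likelihood handling of missing values.
- **That the true power is about 71%.** That is the value for men randomised directly to the two interventions (51.2 per group). The plan pools the usual-care men into this comparison and proposes no analysis without them.
- **That 84% is what the trial will have.** It is the value at maximum planned attrition. Lower losses bring it back towards 87%.

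**What to change.** In the Statistical analysis section, replace 77 per group and 87% with about 72 per group and about 84% power at the maximum planned attrition, counting a 20% loss for the delayed intervention of the usual-care men. Add one clause saying that this assumes every remaining usual-care man takes up the offered intervention, and that power falls if some decline. If the authors did mean the follow-up 20% to include the delayed intervention, they should say so and explain why one rate suits both the shorter and the longer path.

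Specific uptake scenarios and a separate power for the directly randomised men are not needed. The cost is one sentence and a slightly less favourable figure. Sample size, design and analysis stay as they are.

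### Maximum likelihood imputation is paired with complete-data t-tests and ANOVA/ANCOVA, with no step that carries imputation uncertainty into the standard errors; one filled value per missing score would inflate type I error or shrink the effect

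*Protocol article*

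**What the plan says.** All the relevant text is in the protocol article, Statistical analysis.

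- Missing data: "Data will be analysed using an intention-to-treat approach with maximum likelihood imputation of missing values".
- Analyses: descriptive statistics, t-tests, chi-square, correlation and regression, and "two way (group × time) repeated measures ANOVA (or ANCOVA as appropriate) to examine differences between groups over time".
- Error rate: "All tests will be two-tailed and an alpha level of 0.05 will be applied as the criterion for statistical significance".
- Expected loss: earlier trials' experience "indicates an attrition rate of up to 20% over the intervention period", and "we anticipate a further attrition rate of up to 20% over the follow-up period".

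The article does not say whether imputation is single or multiple, which variables enter the imputation model, or how variances are adjusted afterwards.

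**The concern.** Classical repeated measures ANOVA needs a score at every visit for every man. An intention-to-treat version therefore needs the gaps filled first, and the natural reading of the two sentences is to fill and then analyse.

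Complete-data software counts each filled value as an observed man. If a filled value is the model's prediction for that man's own arm, it adds to the sample size and adds no residual scatter. The standard error is then too small on both counts. If the prediction ignores arm, men with missing scores are pulled towards the same expected value in every arm and the treatment difference shrinks.

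At stake are the p-values and confidence intervals for the primary comparisons at 6 months and for the comparison at follow-up.

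**Working it through.** **Inputs from the document.** SD of change about 22 points and difference about 11 points on the QLQ-PR25 sexual activity domain; 64 per group needed; 80 per arm randomised; attrition up to 20% by 6 months and up to a further 20% by follow-up; two-sided alpha 0.05.

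**Assumptions, not in the document.** One fill per missing score; baseline to 6-month correlation of 0 to 0.9; scores missing completely at random.

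**1. The plan's own figures reproduce.** d = 11/22 = 0.5. The normal approximation gives 63 per group; the noncentral t gives 64 (power 80.1%). 64/0.8 = 80 per arm, and 3 × 80 = 240. At follow-up, 240 × 0.8 × 0.8 / 2 = 76.8, the stated 77 per group; power by the t distribution is 86.9%, the stated 87%. So cumulative loss is 1 − 0.64 = 36%, and the plan counts only completers as information. Filled data would enter the analysis as 80 per arm at 6 months and 120 per group at follow-up.

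**2. One fill using arm, closed form.** Let m be the missing fraction and σ² the residual variance.

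- Filled values have no residual, so the estimated variance is about σ²(1 − m).
- It is divided by n, where n(1 − m) men were observed.
- Naive SE² is proportional to σ²(1 − m)/n; true SE² is proportional to σ²/[n(1 − m)]. The ratio of SEs is 1 − m.
- Type I error for a pairwise ANCOVA contrast is 2[1 − Φ(1.96(1 − m))].
 - m = 0.10: 2[1 − Φ(1.764)] = 7.8%
 - m = 0.20: 2[1 − Φ(1.568)] = 11.7%
 - m = 0.36: 2[1 − Φ(1.254)] = 21.0%
- For a three-arm F test (2 numerator df, large-sample cut-off 5.99), the error is exp[−(1 − m)² × 5.99/2]: 8.8% at m = 0.10 and 14.7% at m = 0.20.

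**3. Simulation under the null at 6 months.** Three arms of 80, 2,500 trials per setting (Monte Carlo SE about 0.4 points at 5% and 0.7 at 15%). Ranges are across the assumed correlations; the rows using arm cover both a common model and separate models by arm.

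| Handling | Group × time F | Pairwise t on change | ANCOVA F |
|---|---|---|---|
| One fill using arm, 20% missing | 9.0–14.6% | 7.7–12.6% | 13.8–16.0% |
| One fill using arm, 10% missing | 6.7–9.5% | 6.0–8.1% | 7.8–9.5% |
| One fill without arm, 20% missing | 4.9–5.4% | 4.5–5.3% | 4.7–5.9% |
| Observed men only, 20% missing | 4.2–5.5% | 4.3–5.3% | 4.1–5.6% |

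Using one random draw in place of the predicted mean does not cure this: the group × time F test then rejects in 8.8% to 12.5% of null trials at 20% missing.

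**4. One fill without arm.** Missing men contribute no expected difference between arms, so the expected estimate is (1 − m) × 11. At m = 0.20 this is 0.80 × 11 = 8.8 points. At m = 0.36 a true d of 0.50 becomes 0.64 × 0.50 = 0.32.

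**5. Follow-up.** The comparison there is between two groups, and earlier post-treatment scores exist for some men who later drop out. With two groups of 120, 36% monotone loss, and one fill using arm and the earlier visits, type I error is about 13% to 16% for change scores and about 18% to 22% for ANCOVA.

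**The case against.** The strongest reply is that the harmful details are inferred. The article does not use the words single, one or EM. The phrase could be loose wording for a full-information likelihood analysis, and repeated draws from a likelihood-based model are not excluded. Either would keep the error rate near 5%. A journal article may also leave the choice of imputation model and the variance combination to a full plan that is not shown.

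A reader might infer that the plan does fill once, and that the error rate therefore doubles. The documents do not support that. It needs a single fill, arm in the imputation model, and loss at the 20% ceiling, which the plan gives as an upper limit. At 10% loss the inflation is modest, and without arm there is none. The 21.0% figure also ignores the earlier scores available at follow-up, and that comparison is not the one on which the 64 per group is based.

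These points remove any unconditional claim. They do not remove the point itself. The article names a method and pairs it with procedures that treat filled values as data. A full-information likelihood analysis imputes nothing, and multiple imputation needs a pooling step that is not mentioned. Neither form of single fill is sound: one gives standard errors that are too small, the other a biased estimate.

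**Conclusion.** The point holds in conditional form. As worded, the plan permits an analysis that treats filled scores as observed.

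- **One fill using arm:** type I error at 6 months is about 8% to 16% at the maximum 20% attrition, depending on the test, and 6.0% to 9.5% at 10%. It is higher at 36% cumulative loss.
- **One fill without arm:** the test keeps about 5%, but the estimate and its interval centre on about 8.8 points where the truth is 11.
- **Likelihood analysis of observed data, or properly pooled multiple imputation:** there is no error to report beyond the wording.

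The sizes rest on scores missing completely at random and on assumed correlations. The closed-form figures do not depend on the correlation. The document does not show which of the three cases is intended, so it cannot be said that the reported p-values will be wrong.

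**What to change.** Replace imputation followed by repeated measures ANOVA with a likelihood-based mixed model for repeated measures fitted to all observed scores, with arm × visit, baseline × visit and an unstructured covariance. The alternative is multiple imputation with arm in the imputation model, combined by Rubin's rules. State that singly filled values will not be analysed as observed. If a full-information likelihood analysis was meant, name it in place of imputation and ANOVA. If a fuller plan already specifies one of these, align this sentence with it.

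The cost is a change of wording and standard software, best made before the primary results are analysed. Intervals will be wider than after a single fill, but no planned power is lost: the sample size already counts completers, and 64 observed men per arm give 80.1% power for 11 points with SD 22.
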